### Data collection, management, and analysis

#### Data collection

*Phase 1*. ***Feasibility assessment of FFQ*.** The feasibility of the FFQ will be evaluated in a small number of participants (n = 75) in a ratio of 2:1 consisting of 50 clinical patients and 25 healthcare professionals to ensure adequate saturation in both groups (**Fig 1**). In the feasibility assessment, eligible clinical patients and healthcare professionals will fill out the questionnaire and be asked to provide feedback on the clarity, ease of use, cultural appropriateness and difficulty encountered in answering the questions. Additionally, the healthcare professionals will provide feedback on the clinical relevance and potential impact on patient care and suggest improvements to optimise the questionnaire’s effectiveness. In summary, we will be well-powered to evaluate feasibility from the perspective of patients and clinicians.

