#### Development of FFQ score

The FFQ score will be developed using the participant’s dietary intake captured by the FFQ (**Fig 1**). The scoring system will be undertaken similar to the methods used by Framingham and INTERHEART. Briefly, using a random sub-sample of the study population (e.g., 1/3) as a test group, the intake of all 27 food items for each participant will be converted into tertiles, where 1^st^, 2^nd^, and 3^rd^ tertiles represent low, moderate, and high intake for the food item. The association between tertile scores for each of the 27 food groups and hypertension will be individually evaluated in 27 multiple variable regression models in the test group, adjusted for common covariates (e.g., sex, age, etc.). The beta-coefficients for the food item (rounded to the nearest integer) in each multiple variable model, that is significant (p<0.05), will be used as a ‘weight’ to quantify the individual food item’s contribution to hypertension risk. These food tertiles and their weights with then be used to calculate FFQ scores in the other 2/3 of the study population (i.e., validation group) for each individual and then regressed against measures of hypertension. Correlation matrices and forward stepwise regression models will be checked and used to minimise the effect of correlated food items. If the FFQ score is valid, a significant association will be observed between the FFQ score and measures of hypertension.

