Dietary intake according to the 27-item FFQ will be used to develop an FFQ score based on associations between individual foods and blood pressure using correlation and regression analysis. The result of the regression models will inform the weighting and scoring assignment for each food item in the FFQ. Following the assignment of scores for each individual food item, an aggregation process will be undertaken to obtain an overall dietary score for each participant. The association between the FFQ score and blood pressure will be evaluated using regression analysis, allowing for a robust evaluation of the scoring system’s predictive validity and adjusting for potential confounders, such as age, sex, BMI, physical activity, and socioeconomic status.

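### Forward stepwise item selection is not confined to the test third, so validation-group blood pressure may shape the FFQ score and the Phase 1 validation p-value need not hold its 5% level

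*Protocol article*

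**What the plan says.** Phase 1 has "50 clinical patients and 25 healthcare professionals"; only the patients supply data for validating the FFQ.

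Under Development of FFQ score, the article describes in turn:

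- derivation "using a random sub-sample of the study population (e.g., 1/3) as a test group", with the foods "individually evaluated in 27 multiple variable regression models in the test group";
- weighting: the rounded coefficient for a food "that is significant (p<0.05), will be used as a" weight;
- testing, where the article applies the weights as follows: "calculate FFQ scores in the other 2/3 of the study population (i.e., validation group) for each individual and then regressed against measures of hypertension";
- then: "Correlation matrices and forward stepwise regression models will be checked and used to minimise the effect of correlated food items".

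The section closes by saying that a valid score will show a significant association with measures of hypertension.

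The Statistical analysis section returns to the score. Regression of blood pressure on individual foods informs the weights, "an aggregation process will be undertaken to obtain an overall dietary score for each participant", and regression then evaluates the score's association with blood pressure. No test or validation group is mentioned there.

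**The concern.** A correlation matrix of food items does not involve blood pressure. Forward stepwise regression does: it admits foods according to how well they explain the outcome, so it changes the score using outcome data from whichever patients it is run in. Only the 27 single-food models are tied to the test group. The stepwise sentence comes after the validation-group regression, names no subset and no entry rule, and nothing says that the food list is fixed before the validation regression is run.

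The validation p-value has its nominal 5% error rate only if no validation-group outcome helped choose the foods. If it did, a score unrelated to blood pressure can appear validated in Phase 1. An analyst could run the stepwise step in the test third, in the validation group or in all 50 patients and still comply with the text.

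**Working it through.** **The plan's own figure.** The only computed sample size is 29, for the correlation between FFQ and 24-hour recalls (r = 0.5, two-sided alpha 0.05, power 0.80). By Fisher's z: ((1.960 + 0.842)/0.549)² + 3 = 29.0. It reproduces, with simulated exact power 0.814 at n = 29. No figure is given for the score or for the split.

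**Inputs from the article.** 50 patients; one third is 50/3 ≈ 17, leaving 33; 27 foods in tertiles; food selection at p<0.05; weights rounded to integers; final test at 0.05.

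**Assumptions.** Continuous blood pressure unrelated to diet, SD 18 mmHg (affects only rounding of the weights); adjustment for age and sex; inter-item correlation 0 or 0.3; stepwise entry at p<0.05.

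**Benchmarks by hand, independent items.**
- False foods expected in the test third: 27 × 0.05 = 1.35. Chance of at least one: 1 − 0.95^27 = 75.0%.
- Locked score, per trial: 0.750 × 0.05 = 3.8%.
- Chance that some food is significant in the test third and again in the 33: 1 − (1 − 0.05²)^27 = 6.5% of trials. Per trial with a weighted food: 6.5/75.0 = 8.7%.

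**Simulation.** 5,000 null trials per setting, with the final score always tested in the 33. Each cell gives inter-item correlation 0 / 0.3.

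| Stepwise run in | Foods considered | Weights | Score exists | Significant, of scores that exist | Significant, of all trials |
|---|---|---|---|---|---|
| not run | – | test third | 74.7 / 67.2% | 5.4 / 4.8% | 4.0 / 3.2% |
| test third | already weighted | test third | 74.7 / 67.2% | 5.0 / 4.7% | 3.8 / 3.2% |
| all 50 | already weighted | test third | 22.8 / 21.1% | 15.9 / 16.0% | 3.6 / 3.4% |
| the 33 | already weighted | test third | 6.4 / 6.1% | 96.3 / 96.1% | 6.2 / 5.9% |
| all 50 | all 27 | test third | 75.4 / 67.9% | 54.4 / 48.8% | 41.0 / 33.2% |
| all 50 | all 27 | refitted in 50 | 75.4 / 67.9% | 72.6 / 71.2% | 54.7 / 48.4% |
| the 33 | all 27 | test third | 75.3 / 66.6% | 66.3 / 64.5% | 49.9 / 43.0% |

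The denominator matters in the fourth row. Few scores survive pruning in the 33, and nearly all that do are significant. Taken over trials in which the test third had produced a score, the rate is 6.2/0.747 = 8.3% and 5.9/0.672 = 8.8%. The like-for-like inflation over the second row is 6.2/3.8 = 1.6 and 5.9/3.2 = 1.8 times.

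Further runs, some with five covariates, give 4-6% for the locked score, up to about 12% for pruning in the 33, and 62-75% of scores formed for re-screening all 27 foods there. With no split at all, so that derivation and testing use the same 50, they give 65-77% of trials. That is close to the 75.0% chance of at least one false food, as expected when foods are tested in the patients who selected them.

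**The case against.** A reader might infer that the plan orders stepwise selection on validation data. It does not. The account is explicitly brief, no sequencing word ties the stepwise sentence to the one before it, and its stated purpose (handling correlated foods) belongs naturally to item selection, which the section places in the test group. Reading it as a check within the test third is fair, and on that reading the error rate is nominal.

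A reader might also infer that the Statistical analysis section abolishes the split. It is silent on the split; it does not contradict it. Its evaluation sentence names neither phase nor subset and could refer to the validation group or to Phase 2. The 65-77% figure therefore describes only an analyst who follows that section alone.

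The largest rates with the split kept need all 27 foods to be re-screened outside the test third, which sits badly with the test-group p<0.05 rule. If stepwise selection in all 50 merely prunes foods already weighted, the per-trial rate (3.4-3.6%) is no worse than for a locked score.

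The validity sentence says that a valid score will be significant, not that a significant score is valid, and nothing makes Phase 2 conditional on it. Phase 2 tests the score again in 50 patients. The Recruitment section covers both phases, which suggests new patients, but the article does not say so outright.

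All of this limits the size of the point. What stands is that outcome-driven selection is described with no restriction to the test group, beside a significance statement that is the only Phase 1 criterion given for the score. This goes beyond detail left to a fuller document, because the described sequence, followed literally, lets validation outcomes alter the score.

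**Conclusion.** The concern holds as a matter of what the plan permits. As worded, validation-group blood pressure may influence which foods are in the score, so the Phase 1 validation p-value need not hold its 5% level. Under a null association the false-positive rate is:

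- about 5% of scores formed, if the score is locked after the test third;
- about 8-12% of scores formed (6-8% of all trials), if stepwise selection in the 33 prunes only foods already weighted;
- about 62-75% of scores formed (about 43-50% of all trials), if it re-screens all 27 foods there with test-group weights;
- about 65-77% of trials, if the score is derived and tested in the same 50.

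Here a score counts as formed once the initial selection yields at least one food. The figures rest on the assumed continuous outcome, entry rule, covariates and inter-item correlation of 0 to 0.3; which one applies depends on how the text is read. It would go too far to conclude that a false score will be adopted: Phase 2 may expose it if its patients are new.

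**What to change.** Under Development of FFQ score, state that the correlation-matrix and stepwise step uses test-group data only and comes before weighting. State also that the food list, tertile cut-points and weights are frozen before any validation-group blood pressure is analysed, after which the frozen score is tested in one regression. Under Statistical analysis, state that the Phase 1 association is evaluated only in patients not used to derive the score.

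The cost is a few sentences, with no extra patients or data. In the simulation this restores the nominal level (5.0% and 4.7% of scores formed). The downsides are a weaker apparent Phase 1 association and unstable stepwise selection in about 17 patients.

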### Sample size and sampling technique

The targeted sample size for this study was determined by previous studies evaluating the agreement between food frequency questionnaires (FFQs) and 24-hour dietary recalls. These studies have found correlation coefficients (r) ranging from 0.3 to o.7, indicating moderate to strong agreement between the two dietary assessment methods [23–26]. Based on this evidence, a modest correlation coefficient of *r* = 0.5 is considered a good indicator of validity for determining the sample size needed to evaluate the agreement between our clinical FFQ and 24-hour recall [27]. Using G*Power software [28], a priori sample size calculation was conducted for a two-tailed correlation analysis with statistical power = 0.8, alpha = 0.05, and r = 0.5. The analysis indicated that a minimum of 29 participants would be needed to detect a significant correlation between the FFQ and recall measures.

In addition, recent evidence suggests that a sample of approximately 13 participants is sufficient to reach saturation in qualitative studies with a small number of clear objectives (*See Section 3*.*4*.*2*: *Feasibility assessment of FFQ*) [29]. Therefore, the planned sample of 29 participants will be sufficiently powered to evaluate the qualitative evidence and feedback. Nonetheless, to account for an anticipated dropout rate of 20% as well as to accommodate any potential missing/incomplete data, the target sample size will be increased to 50 participants (**Fig 2**) [30, 31]. Furthermore, 25 healthcare professionals consisting of nurses, dietitians, and clinicians at RSUTH will be purposely recruited to provide qualitative feedback on the food frequency questionnaire.

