### Statistical analysis

Statistical analyses will be conducted using R programming language version 4.3.0 [35] with significance level set at p<0.05. Descriptive statistics will be used to analyse categorical and continuous variables. Categorical demographic variables will be analysed using frequency distribution, while continuous demographic variables will be summarised as mean and standard deviation for normally distributed variables and median and interquartile range (IQR) for non-normally distributed variables. As the frequencies of food groups are not normally distributed, differences in frequencies between the two FFQs (FFQ1 vs. FFQ2) and between the two methods (24 HR vs. FFQ2) in phase 1 will be tested using Wilcoxon’s signed-rank test.

Feasibility and acceptability will be assessed through descriptive analyses, including means and 95% confidence intervals (CI), qualitative feedback, and content analysis of indicators related to the process (e.g., proportion interested, started, completed FFQ) and resource (e.g., time to complete and review, rated performance, and practicality).

The West African Food Composition Table will be used to calculate the nutrient content (macronutrients such as energy, carbohydrates or sugar, proteins, fats, and fibre and minerals such as sodium and potassium) of the foods reported in both the FFQ and 24HR. The mean and distribution of nutrient intakes obtained from the FFQ and 24HR will be calculated, and a comparison will be made to assess the differences using the Wilcoxon signed-rank test. Pearson correlations will be used to calculate the correlation coefficients between the FFQ and 24HR for each nutrient to assess the agreement between the FFQs and 24HR and the reproducibility of the FFQs. Additionally, the agreement between the FFQ and the average of three 24-hour dietary recalls will be estimated using Intraclass Correlation Coefficient (ICC), de-attenuation of the correlation coefficients, or quintile cross-classification analysis and the Bland-Altman plots will be used to visualise the agreement between the recalls and FFQ [36–38].

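### The protocol says a valid FFQ score will reach significance, but in about 27 to 33 patients non-significance does not show that the score is invalid

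*Protocol article*

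**What the plan says.** The section Development of FFQ score takes a random sub-sample, with one third given as an example, and estimates food weights in it. The weights are applied to the remaining two thirds, called the validation group, and the score is regressed against measures of hypertension. The section ends: "If the FFQ score is valid, a significant association will be observed between the FFQ score and measures of hypertension". It gives no interval and no minimum size of association. The Abstract places this work in the analysis of Phase 1 data. The Statistical analysis section runs all tests "with significance level set at p<0.05" and plans to adjust the score model for age, sex, BMI, physical activity and socioeconomic status.

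The only sample-size calculation is in Sample size and sampling technique: "a priori sample size calculation was conducted for a two-tailed correlation analysis", with "statistical power = 0.8, alpha = 0.05, and r = 0.5". Its result is that "a minimum of 29 participants would be needed to detect a significant correlation between the FFQ and recall measures". It concerns the FFQ against 24-hour recall, not the score against blood pressure. Then, "to account for an anticipated dropout rate of 20" per cent and missing data, "the target sample size will be increased to 50 participants".

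For Phase 2, the section Assessment of the FFQ score and hypertension risk plans a logistic regression in 50 patients with an odds ratio, and mentions a correlation of around 0.5 without a source.

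**The concern.** The quoted sentence makes significance a necessary consequence of validity. Its contrapositive is that a score which does not reach p<0.05 is not valid. That inference is sound only if the test almost never misses a real association. A group of about 30 patients gives no such assurance, and no calculation in the article addresses this comparison.

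What is at stake is how Phase 1 is read. A score with a real, moderate association with blood pressure could be reported as having failed validation when the data are merely imprecise. The score is intended for clinical use, so that reading would matter.

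**Working it through.** **Inputs.** 50 patients and 20% dropout (Sample size and sampling technique); example split one third to two thirds (Development of FFQ score); two-sided alpha 0.05 (Sample size and sampling technique; Statistical analysis); five named covariates (Statistical analysis). The true correlations of 0.3, 0.4 and 0.5 are assumptions. Only 0.5 has a counterpart in the article for score and hypertension.

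**Step 1: reproduce the plan's figure.** By Fisher's z, n = ((1.960 + 0.842)/atanh(0.5))² + 3 = (2.802/0.5493)² + 3 = 29.01. The stated 29 is reproduced. Simulated bivariate-normal power at n = 29 is 81%.

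**Step 2: size of the validation group.** 2/3 × 50 = 33.3, about 33. If every dropout is lost to this analysis, 50 × 0.8 = 40 and 2/3 × 40 = 26.7, about 27.

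**Step 3: chance of missing a real association.** Power ≈ Φ(atanh(r) × √(n − 3 − k) − 1.960), where k is the number of covariates; the opposite tail is negligible. Example, r = 0.3, n = 33, k = 0: 0.3095 × √30 = 1.695; 1.695 − 1.960 = −0.265; power 40%, so 60% missed.

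| True r | Missed, unadjusted, n = 33 / 27 | Missed, five covariates (r as partial correlation), n = 33 / 27 |
|---|---|---|
| 0.5 | 15% / 23% | 22% / 33% |
| 0.4 | 36% / 45% | 44% / 55% |
| 0.3 | 60% / 67% | 66% / 73% |

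Unadjusted simulation agrees to within about two percentage points. If hypertension is analysed as yes/no, with an assumed 50:50 split and r read as the correlation with the underlying continuous measure, simulation gives misses of 33% / 43% at r = 0.5 and 73% / 78% at r = 0.3.

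**Step 4: what the subset can detect.** The true correlation giving 80% power is tanh(2.802/√(n − 3)) = 0.47 at n = 33 and 0.52 at n = 27. The smallest observed correlation that reaches p<0.05 is 0.34 and 0.38 respectively.

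**Step 5: what a non-significant result would look like.** An observed r of 0.3 is non-significant at both sizes. Its 95% interval is about −0.05 to 0.58 at n = 33 and −0.09 to 0.61 at n = 27. Each interval contains both zero and 0.5, so neither shows the score to be invalid.

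**The case against.** The strongest reply is that the sentence describes an expectation, not a decision rule, and that the real validation comes later. Much of this stands. The Abstract and Study design assign validation of the score–hypertension association to Phase 2, with 50 patients and an odds ratio. So a reader might infer that the score stands or falls on one p-value in about 30 patients, but the document does not support that. Nor does it say that a non-significant score would be discarded or reworked. Phase 2 is itself only moderately sensitive: unadjusted power at r = 0.3 is about 56% on a continuous outcome and 39% on a binary one (50:50 split assumed).

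Three further limits apply.

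- A reader might say the subset falls below the plan's own requirement of 29. That is true of 27 but not of 33, and the 29 was calculated for a different comparison. The 27 is also a lower end: the Participant timeline collects an FFQ and blood pressure in the first week, so patients who leave later could still contribute. The one-third split is itself only an example.
- At r = 0.5, unadjusted and on a continuous outcome, power is 77–85%, close to convention. Frequent misses depend on a weaker association, on adjustment, or on a binary outcome.
- A reader might infer that any significant result, even in the wrong direction or on one of several measures, would count as validation. The sentence does not state that converse, and the document has no rule that any one measure suffices.

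What the reply does not remove is the sentence itself. As a statement about what a valid score will show in this subset, it is wrong.

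**Conclusion.** The point holds as a fault of inference in one sentence. In a validation group of about 27 to 33 patients, a valid score need not reach significance. Even at r = 0.5 it fails to do so in about 15–23% of trials unadjusted and 22–33% with the five covariates; at r = 0.3 it fails in about two thirds. Non-significance there is inconclusive.

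The size depends on the assumed true correlation, on the example split being used, and, for the lower sample size, on all dropouts being lost to this analysis. The consequence is limited by the Phase 2 estimate, so this is a wording correction worth making rather than a flaw that undermines the study.

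**What to change.** Replace the last sentence of Development of FFQ score with wording such as:

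> The association of the FFQ score with one named blood-pressure measure in the validation group will be reported as a slope and correlation with 95% CI. A CI excluding zero in the expected direction supports validity. A CI including zero is inconclusive and will not be taken as evidence that the score is invalid; the Phase 2 estimate will be read alongside it.

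Add that about 27 to 33 patients give 80% power only for a true correlation of about 0.5 or more. The supportive half of this wording is still a test at 0.05, with a direction added; what changes is the reading of a non-significant result.

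This needs no more patients and no new data. The downside is that the Phase 1 score validation may have to be reported as inconclusive.

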#### Assessment of the FFQ score and hypertension risk

The refined FFQ will be administered to the clinical patients (n = 50) to assess their dietary habits. Individual FFQ scores will be calculated for each clinical patient from their FFQs. A logistic regression will be performed between FFQ scores and hypertension risk (blood pressure), with a correlation coefficient (r) of around 0.5, suggesting a moderate to strong association. The odds ratio will be calculated to quantify the strength of the association between the FFQ score and hypertension.

